# Tennis elbow, study protocol for a randomized clinical trial: needling with and without platelet-rich plasma after failure of up-to-date rehabilitation

**DOI:** 10.1186/s13018-020-01998-8

**Published:** 2020-10-07

**Keywords:** Clinical protocols, Double-blind method, Randomized, Research design, Tennis Elbow, Tendinopathy, Rehabilitation, Extracorporeal shock waves therapy, Platelet-rich plasma, Ultrasonography, Interventional

## Abstract

**Background:**

The conservative management of lateral epicondylitis is known to be a difficult-to-treat annoying condition. A treatment with platelet-rich plasma (PRP) is often performed, but its efficacy remains controversial.

**Methods:**

This study is a single-center, randomized double-blind controlled trial, preceded by a case series. All the 232 planned patients of the case series will undergo an up-to-date comprehensive rehabilitation program, including focused extracorporeal shock waves therapy. This rehabilitation program is expected to have a maximum success rate 75%. It is therefore aimed to allocate a minimum of 58 patients with rehabilitation failure into the 1:1 randomized trial. Stratification is planned on age and lesion pattern. The masking will be quadruple (Participant, Care Provider, Investigator & Outcome Assessor). The patients will undergo an ultrasound (US)-guided needling combined with either PRP (intervention group) or saline (control group). The primary endpoint will be the pain improvement from baseline (month 0) at 3 months on a 0–10 visual analog scale (VAS) during a maximal strength isometric contraction of the extensor carpialis brevis muscle. The main secondary endpoints will include the rehabilitation success rate and improvements from baseline at 3, 6, and 12 months of the following outcomes: (i) Single Assessment Numeric Evaluation (SANE) score, (ii) Patient-Rated Tennis Elbow Evaluation (PRTEE) score, (iii) maximal grip strength on Jamar test, and (iv) the ultrasonographic evaluation of the US of the epicondylar tendons.

**Discussion:**

The study results will provide insight into the effect of PRP as adjuvant therapy to tendon fenestration, and may contribute to identify the best preceding and concomitant rehabilitation protocol.

**Trial registration:**

ClinicalTrials.gov NCT03987256. Registered on 20 August 2019.

## Background

The conservative management of lateral epicondylitis is known to be a difficult-to-treat annoying condition. The first-line conservative management includes physical therapies, orthotics [1], and extracorporeal shock wave therapy (ESWT) [2]. The success rate of ESWT for lateral epicondylitis depends mainly on the protocol that is followed. For instance, poor results have been observed with too low energy [3]. Focused ESWT has been showed to be as effective as surgical tenotomy [4].

Infiltrative therapies might be proposed in case of persistent symptoms. It has been well established that corticosteroids are efficient in the short-term but deleterious in the long-term [5, 6] likely for degenerative purposes [7]. Prolotherapy, autologous blood or botulinic toxin injections, and others infiltrative therapies are less studied and are therefore not clearly supported by the current literature [8–10]. Stem cells might be an appropriate alternative in the future [11].

Platelet-rich-plasma (PRP) is nowadays widely used for tendinopathies, considered as safe, and currently supported by the strongest scientific journals [12]. However, the potential benefits of PRP are discordant, especially concerning the elbow. Even if the superiority of PRP over corticosteroids is well established [13], the efficacy of PRP in addition to tendon needling or fenestration compared to tendon needling or fenestration alone is still controversial [14–19].

Several factors have been advocated to influence PRP outcomes. The most relevant ones are direct mechanical action of the needle and fenestration technique, number of PRP injections, cell counts (platelets, white blood and red blood cells), activation of the platelets, concomitant local anesthetic use, peri-interventional use of NSAIDs and corticosteroids, concomitant rehabilitation, or a contrario immobilization [20]. The positive results observed in the previous reported studies remain debatable as they can be [17, 18] related to either PRP, fenestration [21], or any of the abovementioned confounding factors.

The first aim of this study is to determine the proportion of patients that would need an infiltrative technique after a proper rehabilitation protocol including physical therapies, focused ESWT, and orthotics and Kinesio taping for all patients. Our second aim is to establish whether PRP as adjuvant therapy to fenestration would increase clinical outcomes.

## Methods

### Aims

The clinical efficacy of platelet-rich plasma as adjuvant therapy to tendon needling for patients suffering of epicondylar tendinosis managed with a first line up-to-date rehabilitationThe efficacy of platelet-rich plasma as adjuvant therapy to tendon needling on the epicondylar tendon repairThe clinical efficacy of the first-line rehabilitationThe efficacy of the first-line rehabilitation on the epicondylar tendon repair

### Study design

This study will include 232 patients and will be conducted in two steps (Fig. 1). The first step consists in an observational case series. During this step, all patients will benefit from a proper rehabilitation including epicondylar stretching and eccentric strengthening; periscapular and global tonification; postural adjustment; manual therapies including trigger points release, epicondylar taping, or bracing; and focused shockwave therapy (Additional file 1). The second step consists in a case-control superiority trial randomized 1:1 between PRP (intervention group) and saline (control group) injections. A stratification is planned on age and lesion pattern.

**Fig. 1 Fig1:**
[figure not shown]
Study flowchart

Timelines are presented in Table 1. After 3 to 6 months of rehabilitation, if patients are not satisfied, they will be allocated to the PRP or saline group. The follow-up will last 1 year after the intervention (intervention is at month 0), with endpoints at − 3/− 6, 0, 3, 6, and 12 months of follow-up.

**Table 1 Tab1:** Participant timeline

		Study period								
	Enrolment	Rehabilitation				Allocation	Post-allocation			Close out
**Timepoint in months**	− 3^¼^ to − 6^¼^	− 3 to − 6	− 1^½^ to − 4^½^	0 to − 3	0*	0	¼	3	6	12
**Enrolment**										
Patient information and consent	x									
Informed consent collection		x								
Validation of inclusion and exclusion criteria		x								
Randomization						x				
**Interventions**										
Organize rehabilitation		x								
Rehabilitation checkpoint			x	x	x			x	x	
Needling (with PRP or Saline)							x			
**Assessment**										
Clinical evaluation	x	x								
Elbow echography	x			x	x			x	x	
Demographics		x								
Rehabilitation efficacy assessment				x	x					
Primary outcome assessment								x		
Clinical outcome assessment		x		x	x		x	x	x	x
Concomitant therapy, surgery			x	x	x		x	x	x	x

*Extra rehabilitation visit if rehabilitation lasts > 3 months

### Participants

In this monocentric study, all patients will be recruited into the sports medicine division of La Providence Hospital, Neuchâtel, Switzerland. The following inclusion criteria will be applied: (i) lesion of the extensor carpalis radialis brevis (ECRB) tendon on ultrasonography; (ii) age between 18 and 65 years old; and (iii) written consent obtained following adequate explanation of the study aims, design, and procedures. The following exclusion criteria will be applied: (i) presence of a concomitant pathology that can partially explain the symptoms; (ii) diabetes, immunocompromised status, bleeding disorder, or other significant systemic disease; (iii) corticoids or anticoagulants intake; (iv) anticoagulation therapy; and (v) allergy to local anesthetics.

The informed consent will be obtained by the sponsor-investigator (AS). Other physicians in La Providence Hospital and connected structures in Neuchâtel city (i.e., orthopedists, general practitioners, physiotherapists) are informed of the project. They are kindly requested to refer patients to the sports medicine department.

### Randomization and blinding

The allocation will be performed using computer-generated random number by serials of 4 patients blocks on a 1:1 ratio. Four strata will be used: (i) age 18–39 and absence of lesion on the superficial epicondylar tendon; (ii) age 18–39 and concomitant lesion on the superficial epicondylar tendon; (iii) age 40–65 and absence of lesion on the superficial epicondylar tendon; and (iv) age 40–65 and concomitant lesion on the superficial epicondylar tendon. The sponsor-investigator (AS) will generate 10 computerized allocation sequences. The secretary will randomly select one of those sequences for the study. The sponsor-investigator will enroll the participants and will perform the intervention 3 months after the recruitment. Patients will be allocated to a group at the time of the intervention, and only if the rehabilitation process was not successful. The unblinded co-investigator (MF) will access to the allocation on a sequentially numbered list and prepare the injection for the intervention in an opaque syringe (blinded content for AS). It is worth noting that this co-investigator will not take care of the patients subsequently.

This study is quadruple-blinded. Blinding concerns (i) the participants and (ii) the principal investigator (AS) during the intervention, (iii) the outcome assessment, and (iv) the statistical analysis. A complete masking of the intervention will allow the blinding of the participant and the principal investigator for the intervention and the outcome assessment. First, for all patients, the co-investigator (MF) will perform a blood puncture in room A. He will then go in room B and, depending of the allocation, prepare the PRP or turn-on the centrifuge for 5 min (sham PRP preparation). After that, he will prepare an opaque syringe containing either PRP or saline solution. In room A, the principal investigator will perform the ultrasound-guided fenestration of the ECRB tendon. During the fenestration, he will use the opaque syringe and inject the blinded content into the ECRB tendon. The statistical analysis (iv) will be performed by the principal investigator using a sham allocation list. Once the statistical analysis is completed, the true allocation list will replace the former list.

Unblinding should not be necessary for the security of patients. Indeed, no adverse effects of the PRP (local pain and tenderness, infection) require unblinding for clinical management. Despite this, if unblinding is necessary in case of unexpected circumstance, the co-investigator will reveal the intervention for concerned patients.

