Trial data of the patient will be stored in a coded manner. The names of the patients will not be disclosed on CRF. A sequential unique patient number will be attributed to each patient into the trial and reported on the CRF. Identification of patients must be guaranteed at the center. Identification of the patients will be stored on a sequential list stored in the principal investigator’s secured server. The principal investigator and designated representatives will have access to the coded dataset and the identification list during, at the end, and after the study.

Note: in order to insure the blinding of the principal investigator, the allocation list will only be accessible to the co-investigator (MF), or under request to the informatics crew for backup.

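### The investigator who enrols, injects and analyses also writes all ten candidate allocation lists, so only the choice of one in ten is hidden: an avoidable weakness in concealment, not a shown breach

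*Protocol article*

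**What the plan says.** All of this is in the protocol article.

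- **Generation (Randomization and blinding).** The sponsor-investigator "will generate 10 computerized allocation sequences". Then: "The secretary will randomly select one of those sequences for the study".
- **Structure (same section).** The lists use "computer-generated random number by serials of 4 patients blocks on a 1:1 ratio", and "Four strata will be used", formed from two age bands and presence or absence of a superficial tendon lesion.
- **Roles (same section).** "The sponsor-investigator will enroll the participants and will perform the intervention 3 months after the recruitment". Also: "The statistical analysis (iv) will be performed by the principal investigator using a sham allocation list". The sponsor-investigator and the principal investigator carry the same initials, so they are one person. That this person also assesses outcome is implied, because masking the principal investigator is presented as what blinds the outcome assessment. It is not stated outright.
- **Safeguards.** An unblinded co-investigator prepares an opaque syringe in a separate room, with sham centrifugation for controls, and takes no further part in patient care. Under Data collection and management, "the allocation list will only be accessible to the co-investigator" (or, on request, to IT staff for backup), expressly to keep the principal investigator blind. Under Oversight and monitoring, an external physician checks the randomisation and blinding procedure at the start and later verifies the analysis.

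**The concern.** The custody rule and the sham list are meant to keep the investigator from knowing who received what. Both work less well if that person wrote every list that could be in use. The uncertainty then falls from a very large number of possible sequences to ten. Without the ten lists, one emergency code break reveals one patient. With them, it also rules out about half of the other candidates.

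Two features of the design raise the stakes. First, allocation happens at the intervention, after a judgement that rehabilitation has failed or should run for another three months. Foreknowledge of the next assignment could therefore affect who is randomised and when. Second, the primary outcome is a self-reported pain score during a provoked contraction, which the expectations of whoever conducts the test can influence. With a planned minimum of 58 randomised patients, a few affected entries or ratings would matter.

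**Working it through.** **Inputs.** Ten lists, blocks of 4, 1:1 allocation and four strata (Randomization and blinding). Difference of 10 points, SD 10, power 95%, alpha 5%, dropout 10%, rehabilitation success 75% (Sample size). Assumptions: the ten lists are independent permuted-block lists, their author keeps them, and outcomes are normal.

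**The plan's own figure.** Per arm, two-sided: 2 × (1.960 + 1.645)² × (10/10)² = 26.0, so 26. Total 52; 52/0.90 = 57.8, so 58; 58/0.25 = 232. The stated size reproduces, and nothing below changes it.

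**Route 1: known allocations.** Suppose k true allocations from different blocks are known. Each of the nine wrong lists matches all k by chance with probability p = 1/2^k. Then:

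- P(live list is the only match) = (1 − p)^9
- mean probability placed on the live list = [1 − (1 − p)^10] / (10p)

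| k | Only match | Mean probability on live list |
|---|---|---|
| 0 | 0% | 10% |
| 1 | 0.2% | 20% |
| 3 | 30% | 59% |
| 4 | 56% | 76% |
| 5 | 75% | 87% |
| 6 | 87% | 93% |
| 7 | 93% | 97% |

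The chance of full identification passes 50% at k = 4 and 90% at k = 7. A simulation with randomly placed reveals (5,000 runs, lists of 60) agrees: mean 4.7, median 4, 90th percentile 7.

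**Route 2: outcomes, with no code break.** The principal investigator has access to the coded dataset during the study (Data collection and management). Someone holding all ten lists could compute the PRP-minus-saline difference under each. The probability that the live list gives the largest difference (20,000 simulated sets) is:

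| Patients with outcome | Planned effect (10/10 = 1 SD) | Half that effect (assumption) | No effect |
|---|---|---|---|
| 20 | 71% | 37% | 10% |
| 40 | 91% | 52% | 10% |
| 52 | 96% | 60% | 10% |

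Forty is also the point at which the plan re-estimates the SD.

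**Block size.** There are six orderings of two PRP and two saline assignments in a block. If all earlier assignments in the stratum are known, an average of 1.33 of 4 (33%) are certain and the best guess is right for 2.83 of 4 (71%). If none is known, the block size alone leaves the guess at 50%.

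**The case against.** The strongest reply is that the article builds a real barrier around each allocation: a separate preparer, a separate room, sham centrifugation, an opaque syringe and an external check of the procedure. It also says that unblinding should not be needed for patient safety, so four to seven certain reveals are not expected. With no reveals all ten lists stay equally likely. Taking the majority of the ten at each position would be right about 62% of the time (0.5 + 5 × 252/1024/10), which is an edge but not identification. The outcome route is strongest late, when few patients remain to be randomised. Entry to randomisation also depends on patient dissatisfaction, so it is not the investigator's decision alone.

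Most of this stands, and it limits the point to a vulnerability. It does not remove it. The syringe and centrifuge mask each injection; they do not mask lists that the injector wrote. At 20 outcomes, 38 of 58 patients would still be unrandomised or awaiting their result. Late identification still matters for later assessments and for an analysis described as blinded.

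A reader might go further in four ways that the documents do not support:

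- *Concealment is already broken.* Nothing shows that the lists are kept or consulted.
- *The custody rule is contradicted.* It concerns the list in use, and the secretary's draw does hide which one that is, so it holds literally; it protects less than it appears to.
- *The fixed block of 4 by itself makes allocation predictable.* The 33% and 71% figures need earlier allocations that the masking is designed to hide.
- *The investigator certainly performs the outcome test.* This is implied only.

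Nor is this merely detail left to a fuller document: the article states who generates the lists, and that choice is the weakness.

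**Conclusion.** The point holds as an avoidable weakness in concealment and blinding. All candidate lists are written by the person who enrols, injects, analyses and, by implication, assesses, so the protection rests on a one-in-ten draw. Its size depends on two conditions: that the lists remain available to their author, and that either a median of 4 allocations (90th percentile 7) become known or outcomes are examined list by list. The outcome route weakens quickly if PRP does less than planned (91% falls to 52% at 40 patients when the effect is halved) and gives nothing beyond chance if there is no effect. The block size is a secondary contributor. The change is worth making because it is cheap and removes the dependence on the investigator not consulting the ten lists.

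**What to change.** Have the already unblinded co-investigator, or the external monitor who already checks the randomisation procedure, generate one stratified list. It should preferably use randomly varying block sizes that are not disclosed to the sponsor-investigator. The list is held away from that investigator, with the co-investigator keeping the access needed to prepare syringes. Drop the ten-sequence step. State in the text who carries out the outcome assessment.

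The article reports that recruitment began in December 2019. If randomisation has also begun, replace the unused part of the list in each stratum in this way, record the date of the switch, and remove the investigator's access to the ten sequences. Assessment and analysis can then stay where they are, because the person doing them no longer holds the candidates.

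The cost is a short protocol amendment, a small task for existing staff, and slightly larger possible imbalance within strata if block sizes vary. If the monitor generates the list, that person is no longer blind when supervising adverse events, which makes the co-investigator the simpler choice. The sample size stays at 58 randomised and 232 enrolled.

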### Study treatments and interventions

All patients should perform the rehabilitation protocol during the 3 months following the intervention (Additional file 1). During this protocol, all patients will perform global and specific active strengthening and self-stretching, focused ESWT, focused therapies, Kinesio taping, and orthotics. After 3 months, if a constant but insufficient symptom alleviation is observed, the rehabilitation program could be lengthened by 3 months (i.e., rehabilitation months 4–6). If a radiological ECRB lesion persists on ultrasonography, shockwave therapy will be performed during rehabilitation months 4–6. If the rehabilitation protocol enables symptom disappearance (i.e., the rehabilitation was successful), the intervention will not be performed. If, for any other reason, the intervention cannot be performed, the patient will be dropped out of the study.

It is not clear whether PRP should be used or not as an adjuvant procedure to tendon needling. An injection of saline solution during the procedure as comparator seems the most logical, because it (i) allows a proper blinding of both patient and physician, (ii) has no deleterious effects on tendon repair (contrary to active products such as corticosteroids) and therefore no influence on clinical outcomes, and (iii) has no potential side effects.

In both groups, the intervention will occur under strict aseptic conditions as following: First, a local anesthetic blockade of the radial nerve under the arcade of Frohse will be performed under ultrasonographic control. Then, an ultrasound-guided needling of the ECRB tendon will be performed, using the fenestration technique: 25 repetitions with a 20-gauge needle. During the procedure, the lesion will be fulfilled with either PRP (experimental group) or saline solution (control group). The PRP (ACP Arthrex) will be prepared using a double syringe system under the manufacturer’s recommendation. From 15 ml of peripheral blood, the PRP will be extracted on site using centrifugation (1500 rpm 5 min), as recommended by the manufacturer. After the intervention, the learned self-exercises should be continued as long as necessary. The use of ice and pain medication with paracetamol or opioids (tramadol, codeine) will be used to manage pain, if necessary.

No particular measures are planned to improve the adherence to the intervention. The adherence to the rehabilitation protocol will be optimized by the physician, because (i) he will encourage the patient and actively participate to the rehabilitation protocol (Additional file 1) during shockwaves sessions and (ii) at 6 weeks of rehabilitation, the patient will be asked to show the learned active auto-exercises to the physician. Oral corticosteroids, aspirin, and non-steroid anti-inflammatory drugs must be avoided, in spite of their potential deleterious effect on focused shockwaves and PRP. If patients remain symptomatic at the end of the trial, a second needling of the tendon with PRP as adjuvant therapy might be considered. If relevant, a surgical debridement of the lesion will be considered.

### Outcome measurements and assessments

The primary endpoint is the pain improvement between months 0 and 3 on a 0–10 visual analog scale (VAS) during a maximal strength isometric contraction of the extensor carpialis brevis muscle. Rationale: most specific clinical test in order to reproduce pain triggered by the tendon target of the intervention. Most clinical effects of the PRP use are awaited after 3 months of follow-up [18, 22]. The tendon healing will be evaluated with ultrasound in secondary outcomes. It was decided to use clinical parameters as primary outcome, because some pathological elements might persist on ultrasound after healing. Although the sensitivity of ultrasound is high, it does not reach 100% [23, 24].

Secondary endpoints:

Proportion of patients for which the tendon needling is not necessary after rehabilitation protocol

Clinical scores at − 3, 0, 3, 6, and 12 months of follow-up: (i) pain on a 0–10 (VAS) during a maximal strength isometric contraction at other timepoints; (ii) pain on a 0–10 VAS scale at rest; (iii) Single Assessment Numeric Evaluation (SANE) score; (iv) Patient-Rated Tennis Elbow Evaluation (PRTEE) score; and (v) maximal grip strength on Jamar test.

Ultrasonographic aspects of the epicondylar tendons at − 3, 0, 3, 6, and 12 months of follow-up: (i) volume of the lesion in mm^3^; (ii) Doppler reaction classified at the proportion of the tendon marked with the Doppler signal; (iii) solution of continuity in mm^3^; (iv) tendon thickness in mm; (v) concomitant superficial lesion and volume in mm^3^; and (vi) pain on a 0–10 VAS scale during sonopalpation.

It is worth noting that all post-intervention outcomes will be compared to their baseline values at month 0 in order to evaluate their net improvements.

